**ABSTRACT**

**Background:** Carcinoma of the cervix is the most prevalent gynaecological malignancy in our environment, and it is associated with significant morbidity and mortality. Papanicolaou test is a well-recognised and efficient screening modality but the uptake of Pap smear in our environment remains poor. Fear of pain from speculum insertion during vaginal examination has been noted as a factor that may reduce the compliance of women to cervical cancer screening and repeat testing. Speculum lubrication may help to reduce these pain and discomfort, but there are fears of its interference with cytological results.

**Aim and Objectives:** To determine and compare adequacy of cervical cytology smears and mean pain scores of women undergoing cervical screening with or without speculum lubrication.

**Research Methodology:** This proposed work will be a randomized controlled study among women having cervical cancer screening at the gynaecological clinic of Nnamdi Azikiwe University Teaching Hospital, Nnewi. Sixty-six patients would be randomly assigned to the ‘Gel group’ and another 66 patients to the ‘No Gel’ group. Samples will be collected from each participant for Pap smear with lubricated vaginal speculum for the ‘Gel group’ and non-lubricated vaginal speculum for the ‘No Gel group’. Pain scores will be assessed with the numeric rating scale for pain. The primary outcome measures will be the mean numeric rating scale pain scores and proportion of women with inadequate cervical cytology smears.

**Handling of Results:** The Statistical Packages for Social Sciences (SPSS) would be employed for data analysis. Statistical test of significance would be deduced at p-value less than 0.05.

**Strengths and Limitations: T**his proposed study is the first of its kind in Nigeria. Conclusions may not be generalized to other types of lubricant gels since only one type of lubricant gel will be used. The histopathologist and the study participants will be blinded hence double-blind.

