**CHAPTER FOUR**

**RESEARCH METHODOLOGY**

4.**1 STUDY DESIGN**

The work will be a randomized controlled study.

4.2 **STUDY SETTING**

This work will be done in the gynaecology clinic of Nnamdi Azikiwe University Teaching Hospital (NAUTH) Nnewi, Anambra State Nigeria. NAUTH is the only federal teaching hospital in Anambra State, a state in the South eastern part of the country. It offers comprehensive and tertiary services to occupants of Anambra, Enugu, Delta, Imo and Abia states. It is structured to offer medical undergraduate and medical postgraduate training as well as paramedical training. It is also well grounded in medical research. This teaching hospital is well equipped to offer obstetric, gynaecological and gynae-oncology services both on in-patient and outpatient bases. Nnewi is one of the biggest towns in Anambra state and consists of 4 villages which include Nnewichi, Uruagu, Umudim, and Otolo. ^41^ It is a place known for its industrial and commercial activities. It is home to the popular Nkwo Nnewi market, the biggest market for motorcycle spare parts in West Africa.^41^ It is home also to major automobile, petrochemical and cosmetic industries and the first indigenous car producing plant in Nigeria. The inhabitants are mainly Christians who speak Igbo majorly and are mostly traders.

4.**3 SAMPLE SIZE DETERMINATIONf**

The sample size will be calculated using the formula for sample size Determination of minimum sample size for experiemtal studies (Difference in proportions) ^42^ substituting for the values of proportion of unsatisfactory smears as found in a previous study ^20^

n **=** [(Z**_β_** + Z**_α/2_**)^2^ x 2P(1−P)] **=** Minimum sample size

E ^2^

Where

P **=** (P_1_ + P_2_) / 2 **=** (0.01+ 0.005) / 2 **=** 0.0075

E **=** Effect size **=** P_1_ - P_2_ **=** 0.01- 0.005 **=** 0.005

Z**_β_ =** Corresponding Z value at 80% Power **=** 0.84

Z**_α/2_** **=** Corresponding Z value at 95% confidence level **=** 1.96

n **=** [(0.84 + 1.96)^2^ x 2(0.0075)(0.9925)] **=** 0.116718 **=** 4668.72 **≈** 4669

(0.005) ^2^  (0.005) ^2^

Adjusting for finite population, N = 60 samples from clinic in 3 months.

n_s_ **=** n^1^ / 1 + n^1^/N

Where;

n_s_ **=** Adjusted sample size

n^1^ **=** Calculated sample size

N **=** population for study

n_s_ **=** 4669 / (1 + 4669/60) = 4669/78.82 = 59.2 **≈** 60

This will be approximately 60 making a total of 120 with 60 controls and the other 60 for intervention arm.

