However, considering attrition rate of 10.0% will give 6 subjects, there will be 6 women in each of intervention and control groups. Therefore, the total number of subjects in each arm = 60 + 6 = 66. So a total of 132 subjects will be recruited for the study.

4.4 **ETHICAL CONSIDERATIONS**

Ethical approval will be gotten from the Ethics Committee of Nnamdi Azikiwe University Teaching Hospital Nnewi before embarking on the study. An informed consent will be gotten from patients before they are selected to participate in the research. The women will choose to take part in the research or withdraw at any time and will be assured of getting standard quality of care without prejudice. The researcher will fund the research and none of the participants will pay for the procedure or investigation. There will be minimal discomfort to the participants. The research assistants and participants will not be given incentives. Information gathered from this study will be treated as strictly confidential.

4.5 **STUDY POPULATION**

The women will be recruited from consenting patients who are at least 25years old who present to the gynaecological clinic of NAUTH Nnewi for routine Pap smear.

4.6 **INCLUSION CRITERIA**

The participants will include pre and post-menopausal women who require Pap smear.

4.7 **EXCLUSION CRITERIA**

The following women would be excluded from the work virgins, pregnant women, women having their menstrual period, women with any overt cervical pathology, women with vulvar pathologies or those on hormone replacement therapy. Women with vaginitis, those undergoing vulvectomy or vaginectomy and women who had fertility-sparing surgery will not be recruited.

4.8 **DATA COLLECTION**

Training will be organized for five Senior Registrars who will work as research assistants. The researcher and the 5 trained research assistants will collect data from the participants at the gynaecological clinic with the aid of a proforma. NAUTH runs outpatient services on every working day and emergency services for 24 hours every day. On the average 2 smears are collected each day for cervical cancer screening in the gynaecological clinic making 10 in a week and 40 samples in a month. So it is expected that the sample size of 102 will be achieved in 3 months.

4.**9 SAMPLING APPROACH, RANDOMIZATION AND ALLOCATION SEQUENCE**

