Purposive sampling approach will be employed. Following informed consent, selected women will be assigned at random into two arms, namely the gel group and no gel group with the aid of computer created sporadic numbers. The sequence of randomization will be generated by tfhe computer via randomly permuted blocks (blocks of 4, allocation ratio 1:1). An independent person will perform the randomization and will not be involved in the study. The independent person will create a randomization table using computer software program available at <http://mahmoodsaghaei.tripod.com/Softwares/randalloc.html>. Serially numbered opaque sealed envelopes will be used for allocation concealment. The study interventions would be printed in a sheet of paper put in serially numbered opaque closed envelopes. The envelopes would be kept and opened by an independent person. Once the envelope is opened the allocation of the participant would not be changed. Each of the envelopes will contain either a sheet of paper showing gel group (Group A) placing the patient into the group using the speculum lubrication or a paper displaying no gel group (group B) placing the patient into the group receiving dry speculum (without speculum lubrication). Participants cannot be switched from one group to the other once they are placed in a group.

4.10 **STUDY PROCEDURE**

The consent for Pap smear will be gotten for each person during the visit. After explaining the procedure, the woman will be placed in dorsal position with the legs flexed at the knee and adducted at the hips.

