**TABLE 4: WILLINGNESS TO COME FOR REPEAT TESTING**

| Willingness to come for repeat testing | ALL | GEL | NO GEL | P VALUE |
| --- | --- | --- | --- | --- |
| YES |  |  |  |  |
| NO |  |  |  |  |

FIGURE 1. NUMERICAL RATING SCALE FOR PAIN

4.13 **STRENGTH AND LIMITATIONS OF THE STUDY**

This study is the first of its kind in a low income country like Nigeria, The limitation is that only one type of water- based lubricant will be used so results may not be applied to other kinds of lubricants. Perception of pain is complex and multifactorial. Cultural and genetic factors can affect these results in different populations.

Pap smear collection is provider technique dependent. Even though the researcher and research assistants will all be senior resident doctors with same level of training and experience, there still may be chances of inter provider differences. Except for the histopathologist, the researcher, research assistants and patients will be aware of the intervention assignment because given the nature of the intervention technique, blinding of participants and researcher/ research assistants will be difficult.

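### A single block size of 4, printed in the protocol and used by unblinded staff in one clinic, lets up to one allocation in three be deduced in advance

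*Protocol*

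**What the plan says.** Protocol section 4.9 has the computer generate the sequence by "randomly permuted blocks (blocks of 4, allocation ratio 1:1". It names no second block size, and nothing in the protocol withholds the size from the people who recruit. On selection it states: "Purposive sampling approach will be employed". The order is consent first, then assignment: "Following informed consent, selected women will be assigned at random into two arms". Concealment is by serially numbered, opaque, sealed envelopes, which an independent person keeps and opens.

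Section 4.2 names a single site: "This work will be done in the gynaecology clinic of Nnamdi Azikiwe University Teaching Hospital (NAUTH) Nnewi". No stratification is stated, so one list runs throughout. Section 4.8 gives the staffing: "The researcher and the 5 trained research assistants will collect data from the participants at the gynaecological clinic". It also puts the flow at about two smears a day.

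On blinding, section 4.13 states: "Except for the histopathologist, the researcher, research assistants and patients will be aware of the intervention assignment". The Abstract differs: "The histopathologist and the study participants will be blinded hence double-blind". That conflict concerns participants only. Neither passage claims that the operators are blinded.

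Mean numeric rating scale (NRS) pain is one of the two primary outcomes (section 4.11).

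**The concern.** An envelope hides the next slip. It does not hide what follows from the slips already opened once the block length is known. In a 1:1 block of 4, two like allocations at the start fix the next two, and any three fix the fourth. The people who apply gel or use a dry speculum see each allocation as it is delivered. At about two smears a day a block lasts about two working days, which makes tracking feasible.

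Selection takes place before assignment and is purposive. If the arm that is due can be deduced, a recruiter could, knowingly or not, favour women expected to feel more or less pain when a given arm is next. Pain is a subjective primary outcome, and such steering would move the difference in mean scores without any effect of the gel.

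**Working it through.** The protocol gives no figure for predictability, so there is none to reproduce. Its sample size sets the scale: 60 + 6 = 66 per arm (section 4.3), 132 in total, and 132 / 4 = 33 complete blocks.

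**Certain allocations.** A 1:1 block of 4 has 6 permutations. In 2 of them (AABB, BBAA) the last two places are certain. In the other 4 only the last place is certain.

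- Per block: (2 × 2 + 4 × 1) / 6 = 1.333
- Share: 1.333 / 4 = 33.3%
- Of 132: 33 × 1.333 = 44

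**Best guess.** Guessing the arm with more places left, and tossing a coin at a tie, is right with probability 1/2 at place 1, 2/3 at place 2, (1/3 × 1 + 2/3 × 1/2) = 2/3 at place 3, and 1 at place 4. The mean is (0.5 + 0.667 + 0.667 + 1) / 4 = 70.8%, against 50% for unpredictable allocation.

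**Partial knowledge.** Suppose an operator knows each earlier allocation with probability 1/k and also knows where blocks start. An allocation is certain only if both uses of the exhausted arm were seen, so the share is (1/3) / k².

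- k = 1 (full tracking): 33.3%
- k = 2 (knows half): 8.3%
- k = 6 (one of six, no sharing): 0.9%

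The best-guess rates, by enumeration, are 70.8%, 59.9% and 53.8%.

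**Illustrative bias.** Assume that recruiters shift the expected pain of the woman enrolled by δ SD, in opposite directions according to which arm they guess is next. With best-guess rate g, bias = 2δ(2g − 1). The range δ = 0.10 to 0.25 is an assumption; the protocol gives no basis for it. With 60 per arm the standard error is √(2/60) = 0.183 SD, and type I error = Φ(−1.96 + bias/0.183) + Φ(−1.96 − bias/0.183).

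| Observer | g | Bias (SD) | Type I error |
|---|---|---|---|
| Blocks of 4, full tracking | 70.8% | 0.083 to 0.208 | 7.4% to 20.7% |
| Blocks of 4, knows half | 59.9% | 0.040 to 0.099 | 5.5% to 8.4% |
| Blocks of 4, one of six, no sharing | 53.8% | 0.015 to 0.038 | 5.1% to 5.5% |
| Random blocks of 6, 8, 10; full tracking, set of sizes known | 66.2% | 0.065 to 0.162 | 6.5% to 14.4% |

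The last row comes from simulating sequences of 132 with an observer who updates on every past allocation. Certain allocations fall to 1.7%.

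**Scale in points.** At an assumed SD of 1.6 (section 2.5 cites a trial with pain-score SDs of 1.17 to 1.71), the full-tracking bias for blocks of 4 is 0.083 × 1.6 = 0.13 to 0.208 × 1.6 = 0.33 points. A numeric-scale trial cited in the same section found a difference of 2.3 − 1.6 = 0.7.

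**The case against.** **Allocation is concealed.** An independent person generates the list and keeps and opens the envelopes. This is a genuine safeguard against reading or swapping slips, and it should stay. It does not address deduction.

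**One in three is an upper bound.** A reader might infer that the six operators know every past assignment. The protocol does not say so. Section 4.13 can be read as each person knowing the women she handles, and no shared log is described. This objection stands, which is why the lower rows of the table belong with the headline figure. The operators can know the sequence, and nothing in the protocol prevents sharing.

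**The bias is hypothetical.** The full-tracking rows need all recruiters to follow the list and steer in one direction throughout. No steering gives no bias. This also stands: the figures show exposure, not an expected result.

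**There is little room to choose.** Section 4.8 implies about 40 smears a month, or 120 in three months, against 132 to be recruited; section 4.3 uses 60 in three months. Most eligible women would be needed, and purposive sampling may mean no more than taking eligible attenders. That narrows the opening. It does not close it, because no rule of consecutive enrolment is stated.

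**The damage could be detected.** A reader might infer that no analysis could reveal such steering. That goes too far. Dummy Table 1 compares age, parity and menopausal status by arm. With a known block size, each woman's predicted allocation probability can also be rebuilt and tested against outcome (the Berger–Exner test). Still, Table 1 contains no measure of baseline pain or anxiety.

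**The remedy is partial.** By the same formula, (2 × 0.662 − 1) / (2 × 0.708 − 1) = 0.324 / 0.417, so about 78% of the computed bias remains for an observer who knows the set of sizes. This is correct, and it is why non-disclosure must be part of the change.

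**Conclusion.** The point holds as a weakness in the design that is cheap to reduce. The share of allocations certain in advance is exact under its conditions: 33.3% (44 of 132) for someone who knows the block starts and all earlier allocations, about 8% for someone who knows half, and about 1% for one of six who never share. Operators are unblinded whichever blinding statement is correct, so the conflict between the Abstract and section 4.13 does not affect this.

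The consequence for the pain comparison is conditional. At most, with full tracking and a consistent assumed shift of 0.10 to 0.25 SD, type I error would be about 7% to 21%. Varying the block size as random 6, 8 and 10 nearly removes certainty (about 2%), but leaves type I error at about 6% to 14% for an observer who still knows the set of sizes. The documents do not show that bias will occur, and the design is not invalidated.

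**What to change.** In section 4.9, replace the single block size of 4 with a statement that block sizes vary at random and that the independent person generates and holds them. Sizes such as 6, 8 and 10 would serve. Do not print them in the protocol or in any other document that the researcher and assistants can see; keep them in a file that only the independent person holds. Non-disclosure is an essential part of the protection, not an optional extra. The envelope procedure stays as it is.

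The cost is one sentence and a new list before the envelopes are prepared. If recruitment stops inside a block of 10, the arms can differ by at most 5 women. The loss of power is negligible: at 132 women a split of 68 and 64 is equivalent to 2 × 68 × 64 / 132 = 65.9 per arm instead of 66.

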Latex gloves will be worn by the researcher or trained research assistants and 2mls of KY jelly (Dionel, Maryland -USA) will be applied on the entire external surfaces of the metal Cusco’s speculum and inserted gently into the vagina to reveal the cervix in women assigned to the gel group. Appropriate size of Cusco’s speculum will be determined for each participant. A dry speculum (no lubricant) will be used for the control group. In all women, speculum insertion will be done as follows: first, the labia majora and minora will be parted to put in the speculum, which will be introduced at an angle of 45-degrees facing downward and then horizontally rotated. After full insertion, the bills of the speculum will be opened until the vaginal cuff is seen and the speculum is fastened by screwing of the thumbnut. A cotton tipped swab will be used to clear any mucous on the cervix. A cytobrush (Diapath S.p.A Martinego, Italy) will be used to take the sample for Pap smear, after obtaining the sample, the head of the brush is removed and put into the liquid preparative collection vial containing a liquid based medium. (Diapath S.p.A Martinego, Italy) The specimen in the vial will then be carefully mixed in the liquid based medium. Then, the speculum will be gently withdrawn. The patient will be cleaned and counselled on the outcome. In addition, after each smear the patient will be asked to rate her discomfort at the end of the procedure on the Numeric Rating Scale for pain with numbers starting from 0 (no discomfort) to 10 (most discomfort). The patient will also state if she will be willing to come for repeat testing in the future. Numeric Rating Scale for pain will be used because it is authenticated and is widely accepted to be appropriate for evaluation of pain. ^20^

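### Six operators who know the arm may examine any woman, and nothing requires the operator to be named before the envelope is opened or recorded afterwards, so operator could differ by arm and bias mainly the pain comparison

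*Protocol*

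**What the plan says.** All places are in the protocol.

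- **Section 4.8** sets the number of operators at six: "The researcher and the 5 trained research assistants will collect data from the participants". The assistants are senior registrars who will be trained for the study.
- **Section 4.9** uses unstratified permuted blocks of 4 and serially numbered sealed envelopes. "The envelopes would be kept and opened by an independent person". What is protected from then on is the woman's arm: "Once the envelope is opened the allocation of the participant would not be changed", and "Participants cannot be switched from one group to the other once they are placed in a group". Nothing is said about who will examine her or when that is settled.
- **Section 4.10** gives the examination to any of the six: "Latex gloves will be worn by the researcher or trained research assistants". It scripts the speculum insertion identically for both arms.
- **Section 4.13** states that "Except for the histopathologist, the researcher, research assistants and patients will be aware of the intervention assignment". It calls smear collection dependent on provider technique and, after noting that all operators are of equal seniority, adds that "there still may be chances of inter provider differences".
- **Appendix 2 (proforma)** has no field for the operator, and dummy Table 1 in section 4.12.1 has no operator row.

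**The concern.** Randomisation balances, in expectation, only what is fixed before it. If the examiner is settled after the envelope is opened, by people who know the arm, operator is no longer among those things. Operator technique bears on pain during speculum examination and on the quality of the sample, and these are the two primary outcomes in section 4.11. The blinded histopathologist protects the reading of the smear. That blinding protects neither its collection nor the pain score.

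If one operator sees more women in one arm and her patients tend to score lower, the arm difference mixes gel with operator. With no operator field on the proforma, such an imbalance would be neither visible in the trial data nor open to correction at analysis.

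**Working it through.** **1. The order of events.** Section 4.9 describes consent, allocation and envelope. Section 4.10 describes the examination and allows any of 1 + 5 = 6 operators. Neither section places the choice of operator before or after the opening of the envelope. The order is therefore open, not stated to be wrong.

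**2. Inputs for the size.** The plan gives no figure for an operator effect, so there is none to reproduce.

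- From the protocol: 60 evaluable women per arm (4.3); two-sided 5% (z of 1.96 in 4.3, threshold in 4.12.1); a reference pain difference of 2.3 − 1.6 = 0.7 point from a reviewed trial (2.5).
- SD: section 2.5 prints SDs of 1.17 to 1.71 on a visual analogue scale from another reviewed trial. The protocol gives no planning SD for the numeric rating scale. I assume 1.6 and, as a wider case, 2.5.
- Assumed: one operator's share of women differs between arms by 20 to 40 percentage points, and her patients score 0.5 to 1.0 point lower.

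**3. Bias.** False arm difference = share difference × operator effect.

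- 0.2 × 0.5 = 0.1 point (0.1/0.7 = 14% of the reference difference)
- 0.4 × 0.5 (or 0.2 × 1.0) = 0.2 point (29%)
- 0.4 × 1.0 = 0.4 point (57%)

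**4. Error rate when gel has no effect.** SE = SD × √(2/60), which is 0.292 at SD 1.6 and 0.456 at SD 2.5. The rejection rate of the two-sided t-test comes from the noncentral t with 118 degrees of freedom and noncentrality bias/SE.

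| False difference | SD 1.6 | SD 2.5 |
| --- | --- | --- |
| 0.1 | 6.3% | 5.5% |
| 0.2 | 10.4% | 7.2% |
| 0.4 | 27.4% | 14.0% |

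**5. How extreme the top row is.** If the six share the work equally, each sees 1/6 of the women. The largest possible share difference is then 2 × 1/6 = 33 points (33% v 0%). A 40-point difference needs an operator who does at least 20% of all examinations, and at exactly 20% she would see one arm only.

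**6. What recording the operator would allow.** I simulated the worst case: 60 per arm, SD 1.6, operator effect 1.0, share 45% v 5%. Without an operator term the mean false difference is 0.40 and the error rate about 26%. This is slightly below 27.4% because operator differences add to the spread. With an operator term the mean difference is about 0 and the error rate about 5%.

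**7. What naming the operator first would leave.** The expected share difference is then 0. Its chance SD with 66 per arm is √(2p(1−p)/66): 0.065 for p = 1/6 and 0.087 for p = 1/2. That is ordinary random imbalance.

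**8. Adequacy.** At the planning rates in 4.3 (0.5% and 1%), 60 women give 60 × 0.005 = 0.3 and 60 × 0.01 = 0.6 expected unsatisfactory smears. At those rates an operator imbalance could hardly move this comparison.

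**The case against.** The strongest reply is that this argues from silence. No sentence says the operator is picked after allocation; the order is only suggested by 4.9 preceding 4.10. The operators are of equal seniority, the assistants are trained, and insertion is scripted. At about two smears a day (4.8) the six need not be present together, so the choice at the moment of allocation may be narrow. This stands as a limit on how likely and how large the bias is. It does not close the gap, because 4.13 itself says differences may remain after those safeguards.

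A second reply is that adjusting for operator would be enough. For a simple operator imbalance that is correct, as step 6 shows. A reader might infer that gel and operator could never be separated afterwards; that is too strong. Adjustment needs an operator record, however, and the proforma does not collect one. Nor would adjustment deal with a choice that depends on both the arm and the woman, such as handing over a woman expected to be difficult only when she is drawn to one arm.

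A third reply is that the analysis plan, which is not shown, may cover this. It could add an operator term, but the order of operator choice and envelope opening is trial conduct and belongs in 4.9 and 4.10.

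**Conclusion.** The gap is real and modest. Six operators who know the arm may examine any woman, the protocol does not require the operator to be named before allocation is revealed, and the operator is not recorded. The comparison mainly at risk is pain. Under the stated assumptions the false difference is 0.1 to 0.4 point and the error rate about 5.5% to 27%. The lower end is negligible and the upper end is an extreme case.

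Two stronger readings are not supported. A reader might infer that operators will be chosen by arm; the protocol does not say so. A reader might also infer a material bias in smear adequacy; at the protocol's own planning rates there are too few expected events for that. The conclusion that the route is open rests on the text alone, while its size rests wholly on assumed operator effects and share differences. It merits a change because the change costs almost nothing.

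**What to change.** In sections 4.9 and 4.10, state three things:

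- The examining operator is named on the proforma before the independent person opens the envelope.
- That operator performs the examination whichever arm is drawn.
- Any later change of operator is recorded with its reason.

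Add an operator field to the proforma in Appendix 2. The recorded operator then allows an operator-adjusted analysis, which removes simple imbalance. Naming the operator first also prevents a choice that depends on both the arm and the woman.

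The cost is a few lines of text and one form entry, with no extra staff or patients and no change in sample size. The downside is that an operator called away must be replaced and the replacement logged.

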The vial will then be taken to the histopathology laboratory of Nnamdi Azikiwe University Teaching Hospital, Nnewi where it would be transferred into a centrifuge tube with same quantity of cleaning solution. The fluid will then be centrifuged for 10 minutes at 1400 rpm; the supernatant will be removed. Smears will be made from the sediments after mixing with the cellular base solution (Diapath S.p.A Martinego, Italy) and stained by the Papanicolaou staining method and reported using the Bethesda system stating whether the sample is satisfactory or not and the reason for unsatisfactory results. Samples will be recorded as “unsatisfactory” if no endocervical cells are present, if they are obscured by blood, or if drying artifact or gel overlay are present; otherwise, they will be recorded as “satisfactory”. ^19^ The histopathologist will not be aware of the intervention arm (group of patients) to which the smears to be analysed belong.

4.11 **OUTCOME MEASURES**

The primary outcome measures will be the mean NRS pain scores and proportion of women with inadequate cervical cytology smears while the secondary outcome measures will be the pattern of Pap smear results and proportion of women willing to come for repeat testing.

4.12 **PLANNED HANDLING OF RESULTS**

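### Section 4.10 writes unscripted counselling ahead of the pain and willingness questions, and the unmasked team that does the smears collects the answers, so contact that could differ by arm is not ruled out.

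*Protocol*

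**What the plan says.** Section 4.10 has the smear taken by the research team: "Latex gloves will be worn by the researcher or trained research assistants". After the speculum is withdrawn, the section turns to counselling: "The patient will be cleaned and counselled on the outcome". Only in the sentence following that does it describe how pain is measured: "In addition, after each smear the patient will be asked to rate her discomfort at the end of the procedure on the Numeric Rating Scale". The item on returning for screening is written after the pain scale: "The patient will also state if she will be willing to come for repeat testing in the future".

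Section 4.8 states who gathers the data: "The researcher and the 5 trained research assistants will collect data from the participants at the gynaecological clinic with the aid of a proforma". Section 4.13 states what they know: "Except for the histopathologist, the researcher, research assistants and patients will be aware of the intervention assignment".

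Section 4.11 makes the pain score co-primary: "The primary outcome measures will be the mean NRS pain scores and proportion of women with inadequate cervical cytology smears". Willingness to return is a secondary outcome there and is objective 3 in section 3.2.

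The proforma (Appendix 2) words both items to the woman herself, with tick boxes. It does not say who ticks them.

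**The concern.** The cytology outcome has a masked assessor. The two outcomes that the woman reports herself have no comparable protection, and they are the ones most open to conversation.

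As the section is written, someone talks to her before she rates her pain and says whether she would come back. That talk has no script and no named giver. Its subject is also unclear, because the vial has not yet gone to the laboratory when the counselling is described. The team collecting the answers knows the arm. Chapter One already argues that inserting a dry speculum cannot be justified, so the study's own text carries an expectation about which arm should do better.

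If reassurance or prompting differed by arm, the pain difference and the willingness difference would both absorb it, and the analysis could not separate it from the effect of the gel. Section 4.13 accepts that masking women and operators is difficult. It does not consider when the questions are asked or by whom, and both can be settled without masking anyone.

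**Working it through.** **What the text fixes and what it leaves open**

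| Point | Stated | Not stated |
| --- | --- | --- |
| Who does the smear | Researcher or trained assistants (4.10) | – |
| Who collects data | The researcher and five assistants (4.8) | Whether the person who examined a woman takes her answers |
| Who counsels | Passive voice (4.10) | The counsellor, the content, any script |
| Order | Counselling, then pain, then willingness, by sentence order (4.10) | An explicit sequence: the pain sentence opens with an additive phrase and is timed only to the end of the procedure |
| Knowledge of arm | Operators and women aware (4.13) | – |
| Contact by arm | Described once, for all women (4.10) | Any difference, and any measure to keep it equal |

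The protocol therefore allows an unmasked operator to counsel a woman and then collect both answers. It does not require this, and it does not say that contact differs.

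**When this biases the comparison**

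Let contact move the mean pain score by a in the gel arm and b in the dry arm. The observed difference is the true difference plus (a − b). If a = b, the bias is zero.

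For willingness, suppose three women in each arm of 66 changed to yes. Each proportion would rise by 3/66 = 4.5 percentage points, and the difference would be unchanged (4.5 − 4.5 = 0). If instead a fraction c of the women who would have said no were won over in both arms, a true difference d would become (1 − c) × d. That is the ceiling effect: it hides a difference and does not create one.

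**Illustration of a differential shift in pain (assumed values)**

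The protocol gives no standard deviation for its numeric rating scale and no size for any shift. Assumptions: 60 women per arm (section 4.3 before attrition), two-sided 5% level, normal approximation, no true effect. A cited trial in section 2.5 reports standard deviations of 1.17 to 1.71 on a visual analogue scale; 1.5 to 2.5 is used here as a range.

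Standard error = SD × √(2/60). False-positive rate = Φ(shift/SE − 1.96) + Φ(−shift/SE − 1.96).

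For SD 1.5 and shift 0.25: SE = 1.5 × 0.1826 = 0.274; shift/SE = 0.913; rate = Φ(−1.047) + Φ(−2.873) ≈ 0.148 + 0.002 = 0.15.

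| Differential shift | SD 1.5 | SD 2.0 | SD 2.5 |
| --- | --- | --- | --- |
| 0 | 5% | 5% | 5% |
| 0.25 | 15% | 11% | 9% |
| 0.5 | 45% | 28% | 20% |
| 0.7 | 72% | 48% | 34% |

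The last row equals the whole difference in the cited trial that used the same type of scale (2.3 − 1.6 = 0.7, section 2.5). It is an upper marker, not an expectation.

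**The case against.** The strongest reply is that the text proves less than a reader might infer. Someone could take section 4.10 to mean that the operators counsel women differently by arm, and always before the questions. The documents do not support that.

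- Cleaning and counselling are described once, for every woman. Where the arms do differ, in gel against a dry speculum, the section says so.
- The counsellor and the asker are both unnamed, and a team of six need not mean that one person examines a woman and also takes her answers.
- The order rests on the sequence of sentences. A rating given as soon as the speculum is out fits the wording equally well.
- The proforma already fixes the wording of both questions.
- That the counselling urges a return visit is also an inference, since only the outcome is named as its subject.

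All of this stands, and it limits the point to a risk that the procedure leaves open. It does not remove the point. Apart from the independent person who holds the envelopes and has no role in data collection, the protocol names nobody outside the smear team who could ask the questions. An unstated order lets counselling come first, and fixed question wording does not control what is said beforehand.

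It is also true that asking earlier does nothing about the woman's own knowledge of her arm. The abstract says otherwise, "The histopathologist and the study participants will be blinded hence double-blind", and the proforma title also calls the trial double-blind. Both conflict with section 4.13 and need reconciling. The point here does not depend on how that is settled, because no passage claims that the operators are masked.

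**Conclusion.** The point holds as an avoidable weakness in a stated procedure. Unmasked team members may collect a co-primary outcome and the outcome for objective 3 after unscripted contact, and nothing keeps that contact equal between arms. Differential influence is possible; it has not been shown.

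Its size is unknown. The false-positive rates above rest on an assumed shift, an assumed standard deviation and no true effect. They show only that a modest differential shift would matter at this sample size. If contact is the same in both arms, the mean pain difference is unbiased, and the remaining worry is lost contrast in willingness. The change is worth making because it protects a primary outcome at almost no cost, not because bias has been demonstrated.

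**What to change.** In section 4.10, state that the woman marks the pain scale and the willingness item herself, in the fixed wording of the proforma, as soon as the speculum is withdrawn and before any counselling. Put the two items on a separate or tear-off page, because the present form also holds eligibility, smear status and the cytology result. Where she cannot read, the wording is read out verbatim, by a team member who did not examine her if one is available.

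Section 4.10 asks about discomfort at the end of the procedure and the proforma about pain during it, so the same edit should bring the two into line.

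The cost is one extra page and slight coordination within the visit. A non-examining reader should stay optional: the clinic averages two smears a day, and the protocol does not say that a second team member attends each one.
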